## Abstract

**Introduction:**

Community-acquired pneumonia (CAP) is a common indication for antibiotic treatment in young children. Data are limited regarding the ideal dose and duration of amoxicillin, leading to practice variation which may impact on treatment failure and antimicrobial resistance (AMR). Community-Acquired Pneumonia: a randomIsed controlled Trial (CAP-IT) aims to determine the optimal amoxicillin treatment strategies for CAP in young children in relation to efficacy and AMR.

**Methods and analysis:**

The CAP-IT trial is a multicentre, randomised, double-blind, placebo-controlled 2×2 factorial non-inferiority trial of amoxicillin dose and duration. Children are enrolled in paediatric emergency and inpatient environments, and randomised to receive amoxicillin 70–90 or 35–50 mg/kg/day for 3 or 7 days following hospital discharge. The primary outcome is systemic antibacterial treatment for respiratory tract infection (including CAP) other than trial medication up to 4 weeks after randomisation. Secondary outcomes include adverse events, severity and duration of parent-reported CAP symptoms, adherence and antibiotic resistance. The primary analysis will be by intention to treat. Assuming a 15% primary outcome event rate, 8% non-inferiority margin assessed against an upper one-sided 95% CI, 90% power and 15% loss to follow-up, 800 children will be enrolled to demonstrate non-inferiority for the primary outcome for each of duration and dose.

**Ethics and dissemination:**

The CAP-IT trial and relevant materials were approved by the National Research Ethics Service (reference: 16/LO/0831; 30 June 2016). The CAP-IT trial results will be published in peer-reviewed journals, and in a report published by the National Institute for Health Research Health Technology Assessment programme. Oral and poster presentations will be given to national and international conferences, and participating families will be notified of the results if they so wish. Key messages will be constructed in partnership with families, and social media will be used in their dissemination.

**Trial registration number:**

ISRCTN76888927, EudraCT2016-000809-36.

Strengths and limitations of this studyThis well-powered multicentre trial will provide new data on efficacy of amoxicillin treatment strategies for uncomplicated community-acquired pneumonia in young children in developed settings in the postpneumococcal vaccine era.The Community-Acquired Pneumonia: a randomIsed controlled Trial (CAP-IT) is one of few randomised controlled trials to measure the impact of differing antibiotic treatment regimens on antimicrobial resistance.The pragmatic approach to eligibility employed by the CAP-IT trial is aligned with clinical practice and so will facilitate rapid knowledge translation.Although determining the optimal endpoint for pragmatic trials is challenging, use of an Endpoint Review Committee in the CAP-IT trial will strengthen the confidence in the results.The generalisability of the CAP-IT trial findings will be maximised by the diversity of the enrolled population, in both severity and setting.

## Introduction

Acute respiratory infections (including community-acquired pneumonia; CAP) are the most common indication for childhood antibiotic use in primary care and emergency departments (ED).^1–3^ Up to 40% of preschool children attend primary care for acute respiratory symptoms, with antibiotics prescribed in 30%.^3 4^ One-third of childhood ED visits are for acute respiratory symptoms or fever; up to 15% are diagnosed with CAP, with highest antibiotic prescription rates in those aged <5 years.^5–7^ ED attendances and hospital admissions for respiratory illness in young children increase annually, and two-thirds of antibiotics for hospitalised children aged 1–5 years are for CAP.^5 8 9^ The healthcare cost of childhood CAP in England is estimated at £8 million/year, though total annual societal costs are up to £17 million.^10 11^

CAP is a differential diagnosis in any child presenting with fever, respiratory symptoms and focal chest signs. No gold standard laboratory, microbiological or radiological tests distinguish bacterial from viral infection; diagnosis and treatment decisions are based on clinical criteria.^12–14^ *Streptococcus pneumoniae* is the most commonly implicated bacterial pathogen, even in settings with routine pneumococcal vaccination (PCV).^15–17^ Children have high rates of bacterial colonisation and carriage of resistant organisms which may be transmitted, with particular risks for vulnerable individuals.^18–21^ Interventions to maintain low antimicrobial resistance (AMR) levels in children may therefore have wider benefits.

Amoxicillin is the recommended antibiotic for childhood CAP in several international guidelines^12 22–24^; however, there are insufficient data to inform dose, duration and impact on AMR. The British National Formulary for Children recommends amoxicillin thrice daily at 40–80 mg/kg/day. Twice daily dosing is widely recommended due to improved adherence and non-inferiority, including by the WHO.^22–26^ Shorter treatment courses are effective in trials performed in low/middle-income country settings, though diagnostic and eligibility criteria limit generalisability of findings.^27 28^ Trials from developed settings predate PCV or include populations with high penicillin resistance rates. There are therefore no robust data to inform treatment duration, leading to variation between 3 and 7 days.^23 24 27–30^ Assessment of treatment efficacy is challenging, as only half of patients recover after 10 days, and 90% take up to 4 weeks to recover fully.^4 31 32^ While ongoing ‘minimal’ symptoms may trigger retreatment (deemed treatment failure) relatively frequently, the most widely used efficacy measure is re-exposure to antibiotics for up to 4 weeks, with recent reported rates of 15%.^29 31 33^

The impact of antibiotics on colonisation with resistant bacteria is complex and dynamic.^34–37^ Insufficiently high dosing could promote selection of resistant pathogens, and while the greatest effect on bacterial load is achieved early, resistant isolates emerge after 4–5 days.^38 39^ Combined effectiveness and resistance data related to antibiotic dose and duration would inform antimicrobial stewardship and childhood CAP treatment strategies.

The Community-Acquired Pneumonia: a randomIsed controlled Trial (CAP-IT) will evaluate efficacy, safety and effect on AMR of different durations and doses of oral amoxicillin treatment for young children with uncomplicated CAP. The specific primary objectives are to determine whether (1) 3 days is non-inferior to 7 days, and (2) 35–50 mg/kg/day is non-inferior to 70–90 mg/kg/day.

## Methods

This multicentre, randomised, double-blind, placebo-controlled 2×2 factorial non-inferiority trial aims to enrol 800 patients over 2 years. Amoxicillin dose and duration are assigned simultaneously, resulting in four treatment arms (figure 1). This protocol has been written in accordance with the Standard Protocol Items: Recommendations for Interventional Trials checklist.^40^

**Figure 1 F1:**
[figure not shown]
Possible treatment arms in the CAP-IT trial. CAP-IT, Community-Acquired Pneumonia: a randomIsed controlled Trial.

### Patient and public involvement

Parents of young children have been involved throughout the development and delivery of the CAP-IT trial. In developing the research question, they advised that shorter antibiotic courses would be welcomed if equally effective, due to difficulties in giving medicine (due to palatability, or challenges with day care and daytime doses). For the same reasons, parents supported twice daily dosing. A key need identified during trial development was support for families, including clear symptomatic safety netting, close contact and availability of a contact number for the local research and clinical teams. Parents reviewed and provided input on all information materials to ensure they were clear and easy to understand. The CAP-IT Trial Steering Committee (TSC) has a parent member, who contributes to discussions as the trial progresses, and will advise on best methods of disseminating results to families as we approach the analysis phase.

### Trial setting

Sites throughout the UK and Ireland are participating from Paediatric Emergency Research in the UK and Ireland (PERUKI; www.peruki.org)^41^ and General and Adolescent Paediatric Research in the UK and Ireland (GAPRUKI; www.gapruki.org.uk). Participating sites are tertiary or secondary hospitals with EDs and inpatient areas where potentially eligible children are managed; participating centres are listed on the trial website (www.capitstudy.org.uk). Centres are selected based on research infrastructure, likely number of recruits, participation in feasibility work and proposed training strategies. Site principal investigators (PI) are qualified by education, training and experience to assume responsibility for proper conduct of the trial.

### Trial population

Participants may be enrolled from EDs, observation units, paediatric assessment units (PAU) or inpatient wards, provided they fulfil eligibility criteria.

#### Inclusion criteria

Children are eligible if they are aged ≥6 months, weigh 6–24 kg, have a clinical diagnosis of CAP (box 1) and will be treated with amoxicillin as the sole antibacterial agent on hospital discharge. Children must have received none or less than 48 hours of treatment with only beta-lactam antibiotics at enrolment.

#### Exclusion criteria

Children are ineligible if they have (1) severe underlying chronic disease (including sickle cell anaemia, immunodeficiency, chronic lung disease, cystic fibrosis), (2) penicillin allergy or other contraindication to amoxicillin, (3) complicated pneumonia (shock, hypotension, altered mental state, ventilatory support, empyema, pneumothorax, pulmonary abscess), or (4) bilateral wheezing without focal chest signs.Box 1Definition of clinical diagnosis of CAPClinical diagnosis of community-acquired pneumonia (CAP) is defined as all of the following:Cough (reported by parents/guardians within 96 hours before presentation).Temperature ≥38°C measured by any method or reported fever within 48 hours before presentation.Signs of laboured/difficult breathing or focal chest signs (one or more of the following):Nasal flaring.Chest retractions.Abdominal breathing.Focal dullness to percussion.Focal reduced breath sounds.Crackles with asymmetry.

### Outcome measures

The primary outcome is clinically indicated treatment with systemic antibiotic other than trial medication for respiratory tract infection (including CAP) up to 4 weeks after randomisation. Reason and clinical indication are adjudicated by an Endpoint Review Committee (ERC), comprising independent and non-independent members. Independent members, including the ERC chair, are paediatricians independent of the trial and not involved in the clinical care of participants. Non-independent members include the chief investigator, project lead and trial physician. ERC members review clinical narrative summaries of retreatment primary endpoint events, supportive data from patient trial diaries, unscheduled visit forms and serious adverse event (SAE) forms; they adjudicate whether additional antibiotics were prescribed due to CAP (early failure, relapse or recurrence), new bacterial infection (respiratory tract infection or other), intolerance of trial medication or another reason. Final adjudication is based on consensus of the independent ERC members.

Secondary outcomes include (1) severity and duration of parent-reported CAP symptoms, (2) specified amoxicillin-related adverse events (AE; thrush, skin rashes and diarrhoea), (3) phenotypic resistance to penicillin at 4 weeks in nasopharyngeal (NP) *S. pneumoniae* isolates, and (4) adherence to trial medication.

### Screening, randomisation, recruitment and consent

The trial flow chart is provided in figure 2. Potential participants may require hospital admission for initial CAP management or may be discharged immediately from an ED or PAU. As antibiotic treatment duration is an eligibility criterion, additional eligibility assessment procedures are undertaken for those receiving antibiotics while in hospital; these differences are outlined in the following sections, and in figures 3 and 4.

**Figure 2 F2:**
[figure not shown]
CAP-IT trial flow chart. CAP-IT, Community-Acquired Pneumonia: a randomIsed controlled Trial.

**Figure 3 F3:**
[figure not shown]
CAP-IT trial schema. CAP-IT, Community-Acquired Pneumonia: a randomIsed controlled Trial; NP, nasopharyngeal.

**Figure 4 F4:**
[figure not shown]
CAP-IT trial assessment schedule (X) indicates tests that may be done if the child’s condition requires it or allows it, but are not mandatory. *Assessments in this column only undertaken for potential participants receiving inpatient antibiotic treatment. †May be done any time before enrolment discussion. ‡Taken before starting antibiotics where possible. CAP-IT, Community-Acquired Pneumonia: a randomIsed controlled Trial.

#### Screening

Potential participants are identified and screened during initial clinical assessment. Participants discharged directly from an ED or PAU undergo all trial procedures prior to discharge. Children given antibiotics while in hospital have a secondary screening episode. Participating centres keep anonymised logs of screened children, including those who were not approached and those who declined participation, which are used to identify any issues for the trial, or at a given site.

#### Consent

Extensive information is available for recruiting sites, including printed and video materials (accessible at www.capitstudy.org.uk); all materials have NHS Research Ethics Committee (REC) approval. Written informed consent is obtained by clinical or research staff from a parent/guardian after explanation of the aims, methods, benefits and potential hazards of the trial. Families may decline participation in all or any aspects of the trial, at any time and for any reason, without incurring any penalty or affecting treatment. Signed consent forms are kept by the site and a copy given to the family. A letter is sent to the general practitioner (GP) informing them of the trial and the child’s involvement.

#### Enrolment process

At enrolment, recruiting staff review trial materials with parents/guardians; these include a symptom diary, participant information sheet (PIS), investigational medicinal product (IMP) administration instructions and contact details for the trial team. The symptom diary collects information on clinical and non-clinical elements including cough, breathing, temperature, AEs, IMP administration, additional antibiotics, any other medication, time off work/childcare and other health service use. Relevant elements are incorporated into baseline data collected by recruiting staff on enrolment clinical report forms. This is done with parents/guardians to facilitate their understanding of diary content; other baseline data include demographics, symptoms, underlying disease, antibiotic exposure in the preceding 3 months, chest findings and quality of life measures. Participants are registered on the online trial database; database access is controlled through authorised usernames and passwords and all patient identifiable details are confidential.

An NP swab is collected at enrolment. *S. pneumoniae* is identified using culture-based techniques, AMR is detected using minimal inhibitory concentration-based techniques and respiratory viruses are detected using molecular techniques. Stool samples are collected in sites participating in ancillary studies, provided specific consent is given. There are no other mandatory radiological or laboratory tests; if done as part of routine clinical care, results of haematological, biochemical and chest radiograph investigations are recorded.

#### Randomisation

Participants are allocated 1:1 to each of the two factorial randomisations, stratified according to whether or not they receive any non-trial antibiotics in hospital before being enrolled. A randomisation list is computer generated based on random permuted blocks by the trial statistician. Based on this list, trial medication (including placebo) is labelled and packaged in a blinded manner by an independent supplier and delivered to trial sites; treatments are randomly assigned by taking the next sequentially numbered treatment from the relevant supply. As it is difficult to taste-match suspensions of amoxicillin and placebo, one brand of amoxicillin is used for all participants for the first 3 days, followed by a second bottle for days 4–7 containing either a second brand of amoxicillin or placebo; both form a yellow-coloured similar tasting suspension, and parents are instructed to expect some change in taste after the first 3 days.

### Trial treatments

Trial treatment starts on the day of enrolment, with the first dose given before discharge where possible. Children receive 3 or 7 days of amoxicillin, and suspension is given twice daily with dosing by weight band; doses are 35–50 or 70–90 mg/kg/day. To ensure blinding, amoxicillin suspensions of different strengths (125 or 250 mg/5 mL) are used so that dose volume is the same regardless of treatment arm.

IMP is stored separately from routine medicines, and is dispensed in a box containing one bottle of amoxicillin and two bottles of either amoxicillin or placebo (blinded to contents). Colour labels indicate which should be used on days 1–3 and days 4–7. The importance of adherence is reinforced when dispensing IMP and during follow-up contacts. Adherence is assessed using the symptom diary, at telephone follow-up contacts, and at final follow-up when families return unused IMP.

IMP may be stopped early for reasons including toxicity, clinical change requiring treatment modification, or withdrawal of consent. All concomitant medications are allowed; if an essential medication interacts with amoxicillin, the IMP is stopped. Although participants are not required to give a reason for discontinuing IMP, a reasonable effort is made to establish this reason.

Situations necessitating unblinding are likely to be rare. Severe allergic reactions occur early during amoxicillin exposure; immediate discontinuation and trigger avoidance is recommended. Delayed reactions are generally mild and resolve with discontinuation. Where retreatment is necessary, unblinding is unlikely to impact on antibiotic choice and is therefore unnecessary. If necessary, unblinding is done using an online emergency unblinding form.

### Follow-up

The trial assessment and follow-up schedule is shown in figures 3 and 4. Telephone contact occurs on days 4, 8–10, 15–17 and 22–24; a face-to-face visit occurs within 2 days of day 29. At each contact clinical signs and symptoms are reviewed, as are adverse treatment effects, acute illnesses requiring medical assessment, new antibiotics and IMP adherence. At each face-to-face visit an NP swab is collected; if there are any CAP symptoms, examination findings and physiological parameters are recorded. If a face-to-face visit is not possible for final follow-up, it is attempted by telephone. If it is not possible to contact families despite reasonable efforts, relevant data are sought from the GP if consent has been given to do so.

Additional healthcare contacts may be necessary. Parents/guardians liaise with the site trial team if they are considering acute clinical assessment during the follow-up period, though they are advised to seek immediate emergency assessment if they feel this is required. Clinician judgement determines whether investigation, treatment or hospitalisation is required. Following any unscheduled assessment, symptoms, health service utilisation and IMP adherence are reviewed by telephone, and face-to-face visits arranged if necessary.

Parents/guardians who discontinue IMP are encouraged to adhere to the follow-up schedule, and the Sponsor is informed. If follow-up is stopped early, data already collected are kept for analysis, and the children are not replaced in the trial. Samples already obtained are processed unless parents/guardians request otherwise.

### Sample size and power

The sample size is based on demonstrating non-inferiority for the primary endpoint for each duration and dose. Although inflation factors have been advocated for factorial trials to account for interaction between the interventions or a reduction in the number of events, this is not necessary if either randomised intervention has a null effect (the underlying hypothesis with a non-inferiority design), as marginal analyses can then be conducted. Assuming a 15% primary outcome event rate, 8% non-inferiority margin assessed against an upper one-sided 95% CI, 90% power and 15% loss to follow-up, 800 children will be randomised. This is considered a minimum sample size; if resources permit, recruitment may continue above this number to increase statistical power and precision, with the approval of the TSC.

### Analysis plan

The primary analysis will be by modified intention to treat (ITT), including all participants who take at least one IMP dose. The primary endpoint will be analysed using time-to-event methods, controlling for previous antibiotic exposure. Potential interaction effects between dose, duration and previous antibiotic exposure will be examined. For some secondary outcomes, including AEs and resistance, on-treatment analyses will be performed as well as ITT analyses.

The primary analysis of the primary endpoint will include only clinically indicated additional systemic antibiotic for respiratory tract infection (including CAP) as adjudicated by the ERC. Sensitivity analyses will be performed to include (1) all systemic antibacterial treatments other than IMP regardless of reason and indication (to guard against bias), and (2) only ERC-adjudicated clinically indicated systemic antibacterial treatment prescribed specifically for CAP (to provide clinical reassurance).

A subgroup analysis will consider CAP severity at presentation, and repeat the main efficacy analysis limited to participants with more severe disease. This will provide reassurance that an overall null effect (if observed) is not due to a dilution effect arising from inclusion of children with mild disease of viral aetiology, an important consideration as CAP is diagnosed clinically.

Lower dose and shorter duration will be considered ‘non-inferior’ to higher dose and longer duration, respectively, if the upper limit of the one-sided 95% CI for the difference in the proportion of children with the primary endpoint at day 29 is less than the non-inferiority margin of 8%. However, inference will be based primarily on point estimates and CIs rather than binary classification of a ‘non-inferior’ or ‘not non-inferior’ outcome.^42^

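### The primary analysis names one covariate, previous antibiotic exposure; adding age and a baseline severity measure would modestly tighten both day-29 risk differences at no data cost

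*Protocol article*

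**What the plan says.** The Analysis plan section of the Protocol article sets time-to-event methods for the primary endpoint, "controlling for previous antibiotic exposure". That variable appears to correspond to the randomisation stratum, since the Randomisation section describes allocation as "stratified according to whether or not they receive any non-trial antibiotics in hospital before being enrolled".

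More is known about each child at entry. The Enrolment process section says "other baseline data include demographics, symptoms, underlying disease, antibiotic exposure in the preceding 3 months, chest findings and quality of life measures". Age is checked for eligibility: "Children are eligible if they are aged ≥6 months, weigh 6–24 kg". Box 1 lists the respiratory signs assessed to make the diagnosis.

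Severity enters the Analysis plan section in a different role: "A subgroup analysis will consider CAP severity at presentation, and repeat the main efficacy analysis limited to participants with more severe disease". The success rule there is set on the day-29 difference in proportions, against a margin of 8%.

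**The concern.** Each factor is judged by one upper confidence limit against 8%. Baseline variables that predict retreatment can absorb part of the outcome variance and bring that limit closer to the estimate without enrolling more children. Age and presenting signs are natural candidates and cost nothing further to collect, but neither is named for the primary estimate. The article itself values precision: it allows recruitment beyond 800 to improve it, and bases inference mainly on estimates and intervals. What is at stake is efficiency in both the dose and the duration comparison. The validity of the analysis is not in question.

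**Working it through.** **Inputs** (Sample size and power section): "Assuming a 15% primary outcome event rate, 8% non-inferiority margin assessed against an upper one-sided 95% CI, 90% power and 15% loss to follow-up", with 800 randomised. Allocation is 1:1 for each factor (Randomisation section), and each factor is compared on all children.

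**1. Reproduce the stated size.** With equal true risks,

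n per group = (1.645 + 1.282)² × 2 × 0.15 × 0.85 / 0.08² = 342 after rounding up.

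That is 684 evaluable children, and 684 / 0.85 = 805 randomised, which agrees with the stated 800.

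**2. Power and precision as planned.** 800 × 0.85 / 2 = 340 evaluable per group.

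- SE = √(2 × 0.15 × 0.85 / 340) = 0.02739.
- Distance from estimate to one-sided upper limit = 1.645 × 0.02739 = 4.51 points.
- Power = Φ(0.08 / 0.02739 − 1.645) = 89.9%.

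**3. Add prognostic covariates.** Let R² be the share of outcome variance that they explain. The variance of the marginal risk difference is then multiplied by about (1 − R²). R² is an assumption, because the article gives no figure for it.

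| Assumed R² | SE | Distance to upper limit (points) | Shrinkage (points) | Power at 800 | Randomised for 90% power |
|---|---|---|---|---|---|
| 0 (as planned) | 0.02739 | 4.51 | – | 89.9% | 805 |
| 0.01 | 0.02725 | 4.48 | 0.02 | 90.2% | 798 |
| 0.02 | 0.02711 | 4.46 | 0.05 | 90.4% | 790 |
| 0.05 | 0.02669 | 4.39 | 0.11 | 91.2% | 765 |
| 0.10 | 0.02598 | 4.27 | 0.23 | 92.4% | 725 |

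Expressed as extra children, 800 / (1 − R²) − 800 gives about 8, 16, 42 and 89 for the four non-zero rows.

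**4. Check the approximation by simulation.** Trials of 680 children with a 15% event rate were simulated, 3,000 per scenario. The adjusted estimate was a standardised risk difference from a logistic model.

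| Odds ratio per SD of the covariate score | c-statistic | R² | Variance relative to unadjusted |
|---|---|---|---|
| 1.5 | 0.61 | 0.02 | 0.97 |
| 2.0 | 0.68 | 0.06 | 0.95 |
| 2.5 | 0.73 | 0.10 | 0.91 |

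The simulated reductions are close to (1 − R²). An R² of 0.10 requires a fairly strong predictor.

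**5. Scale.** The gain applies to the tested quantity only if the adjusted model is averaged back to a marginal risk difference at day 29. An adjusted hazard ratio on its own would not narrow the interval that is compared with 8%.

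**The case against.** The case against is strong in several respects, and most of it stands.

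- **A reader might infer that the plan rules out other covariates.** It does not say so. It names one and is silent on the rest. A journal article condenses, and a fuller list may sit in the analysis plan that is not shown.
- **The stated adjustment is sound.** Controlling for the stratification factor is standard.
- **A reader might take the severity subgroup as evidence that severity predicts retreatment.** The reason given is different: to check that a null result does not come from diluting the comparison with mild viral illness. That concerns variation in treatment effect, whereas a precision gain needs prognosis. The Introduction also says that minimal ongoing symptoms may trigger retreatment fairly often, so a strong link with presenting severity cannot be presumed.
- **A reader might infer that the trial has no slack and needs this gain.** The article calls 800 a minimum and allows more. The 89.9% is the stated 90% after rounding. The calculation also credits nothing to children lost to follow-up, although time-to-event methods use partial follow-up and GP data are sought where consent allows.
- **A reader might fear that chance imbalance in severity biases the result.** Under randomisation it is random error, which the interval already covers.

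What survives is narrower. One covariate is named, others are already recorded, and a standardised adjusted estimator would be somewhat more precise on the same estimand.

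**Conclusion.** The point holds as a small optional improvement. The documents support neither an error nor a contradiction here. Over an assumed R² of 0.01 to 0.05, the gain is about 0.3 to 1.3 points of power per comparison. At R² of 0.10 it is about 2.5 points of power.

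These figures rest on equal true risks of 15%, 340 evaluable children per group, no credit for any precision already gained from the stratum, and a prognostic strength that the article does not give. If age and severity barely predict retreatment, the gain is close to nil. Each factor would benefit to the same extent, because each is analysed on all children.

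**What to change.** Before unblinding, prespecify for the primary analysis:

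- the in-hospital antibiotic stratum, stated explicitly as the meaning of previous antibiotic exposure, because antibiotic use over the preceding 3 months is also recorded and could be read into the term;
- age as a continuous covariate;
- one baseline severity measure from the enrolment form, the same one that defines the severity subgroup.

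Estimate the standardised (marginal) day-29 risk difference, for example by pseudo-observation regression or by averaging model predictions over all analysed children. Compare its upper limit with 8%. Keep the stratum-only estimate as a sensitivity analysis.

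The cost is a sentence or two in the plan and some programming. No new data are needed, and the estimand and margin do not change. If the full analysis plan already lists these covariates with a marginal estimator, nothing more is required.
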